#### Statistical analysis

All analyses will be conducted using R (version 4.3.0) and Python (version 3.10). Continuous variables will be summarized as mean (standard deviation) or median (interquartile range), and categorical variables as counts and percentages. Group comparisons will be performed using analysis of variance or Kruskal–Wallis tests for continuous variables, and chi-square tests for categorical variables. All statistical tests will be two-sided, with a significance threshold of *p* < 0.05. Adjustments for multiple comparisons will be applied as needed.

#### Primary outcome analysis

Associations between baseline variables and time to first incident AMI will be evaluated using Cox proportional hazards regression models. Follow-up time will be calculated from enrolment to AMI, loss to follow-up, death, or end of study. Multivariable models will include prespecified variables, including age, sex, ethnicity, smoking status, systolic blood pressure, diabetes status, lipid profile, and environmental exposures. Additional variables will be selected based on clinical relevance. Continuous variables will be modeled on their original scale, and nonlinearity will be assessed using restricted cubic splines. Hazard ratios (HRs) and 95% confidence intervals (CIs) will be reported. The proportional hazards assumption will be assessed using Schoenfeld residuals.

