### Study population

A total of approximately 2,340 adults will be enrolled from five participating centers, representing Han, Hui, Tibetan, and Kazakh populations across regions with varying altitude, environmental exposure, and healthcare accessibility. Recruitment targets are prespecified according to catchment characteristics, with planned enrolment of 900–1,050 Han, 650–750 Hui, 400–500 Tibetan, and 250–350 Kazakh participants. Sample size estimation is based on an event-driven approach (Supplementary Material 1). Assuming a 4% cumulative incidence of first AMI over 24 months, approximately 80 events are expected, supporting multivariable modeling and subgroup analyses.

Participants will be eligible if they: (1) are aged 30–85 years; (2) have an estimated 10-year atherosclerotic cardiovascular disease (ASCVD) risk ≥20% (6); (3) are permanent residents of the study area (≥6 months per year); (4) provide written informed consent; and (5) agree to repeated follow-up and biospecimen collection. Exclusion criteria include: (1) major comorbid conditions such as end-stage renal disease, hepatic failure, or active malignancy; (2) acute illness at enrolment; (3) severe psychiatric disorders; (4) substance abuse; and (5) pregnancy or breastfeeding (17). Loss to follow-up is defined as absence from more than two scheduled visits or permanent discontinuation. Follow-up will be maintained through clinic visits supplemented by telephone or electronic contact where necessary.

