#### Follow-up assessments

Participants are followed every 3 months over 24 months using a standardized schedule (Table 1). This repeated-measures design allows assessment of temporal changes in risk indicators and their potential association with short-term cardiovascular events. At each visit, symptom status, interim medical events, medication use, and health-related behaviors are updated. Biomarkers are measured at regular intervals, and ECG monitoring is repeated every 6 months. Echocardiography is repeated annually, and CCTA is performed when clinically indicated. All suspected AMI events are adjudicated by an independent, blinded cardiology panel according to the Fourth Universal Definition of Myocardial Infarction (2018) (21).

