#### Environmental and contextual data

Environmental variables, comprising monthly averaged meteorological parameters and air pollutant concentrations, were assigned to each patient according to their residential location and the date of hospital admission. Meteorological metrics, such as temperature, precipitation and relative humidity, were acquired from the ECMWF Reanalysis v5 (ERA5) product, which offers global coverage at a 0.25° × 0.25° gridded resolution (approximately 25 km at the equator) (3). For air pollution exposure assessment, concentrations of fine particulate matter (PM2.5 and PM10) (31), ozone (O3) (32), and nitrogen dioxide (NO₂) (33) were derived from the China High-Resolution and High-Quality Near-Surface Air Pollutants (CHAP) Dataset, which provides estimates at a high spatial resolution of 1 km. Elevation above sea level was also incorporated to account for its potential influence on AMI risk across different altitudes.

Healthcare access indicators include average travel time to the nearest secondary or tertiary hospital, hospital bed density, and physician density per 1,000 population (33). Information on socioeconomic factors, including city-level per capita income, employment patterns, occupational classifications, educational attainment, and housing conditions, will be systematically collected during scheduled follow-up visits and cross-referenced with official statistics from the Gansu Statistical Yearbook issued by the Gansu Provincial Bureau of Statistics, China.

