### Outcomes

The primary outcome is first incident AMI during the 24-month follow-up period. AMI events will be adjudicated according to the Fourth Universal Definition of Myocardial Infarction (2018), based on cardiac biomarker changes together with clinical, electrocardiographic, imaging, and symptom-related evidence. This outcome is defined to capture short-term occurrence of major cardiovascular events within individuals, allowing assessment of variation in near-term risk across populations with different environmental exposures, ethnic backgrounds, and healthcare accessibility.

Secondary outcomes include longitudinal changes in physiological and biochemical indicators, healthcare utilization, and short-term variation in risk markers preceding AMI. Repeated measurements of biomarkers and physiological parameters will be used to evaluate temporal changes within individuals, particularly within the 90 days preceding AMI, to characterize short-term fluctuations in cardiovascular risk. In addition, differences in these trajectories will be examined across environmental and ethnic subgroups to assess population-level heterogeneity in risk patterns.

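### As worded, the loss-to-follow-up rule ends follow-up for participants who miss three visits and come back, so an AMI known to have occurred later would not count

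*Protocol article*

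**What the plan says.** Three statements in the protocol article combine.

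- **End of follow-up** (Primary outcome analysis): "Follow-up time will be calculated from enrolment to AMI, loss to follow-up, death, or end of study".
- **Loss** (Study population): "Loss to follow-up is defined as absence from more than two scheduled visits or permanent discontinuation".
- **Remote contact** (Study population, the next sentence): "Follow-up will be maintained through clinic visits supplemented by telephone or electronic contact where necessary".

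The schedule (Follow-up assessments) is "Participants are followed every 3 months over 24 months using a standardized schedule", which gives eight follow-up visits in Table 1. The time-varying Cox models update their covariates at each visit (Longitudinal and short-term risk analysis), and missing data are to be multiply imputed (Additional analyses).

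On fatal events, Follow-up assessments states "All suspected AMI events are adjudicated by an independent, blinded cardiology panel", applying the Fourth Universal Definition. Outcomes summarises that adjudication as "based on cardiac biomarker changes together with clinical, electrocardiographic, imaging, and symptom-related evidence". Neither section says how a death before any blood sample is routed or classified.

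**The concern.** A missed visit and the end of event follow-up are different things. A missed visit leaves a gap in the covariates. It does not mean that AMI status is unknown, because the participant may attend later, answer the telephone or appear in hospital records. The definition merges the two.

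The stake is events that the study could observe but would not count. Only about 80 are expected, and they must support multivariable models and subgroup analyses. Three unstated details also decide who is lost and from when: consecutive or cumulative misses, the date of loss, and whether telephone contact counts as attendance. Five sites could settle these differently.

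Deaths raise a smaller, related question. If an AMI that kills before sampling is never put forward as suspected, it ends follow-up as a death. Healthcare access is one of the study's subgroup factors and is measured partly by "average travel time to the nearest secondary or tertiary hospital", so recognition of fatal AMI would need to be similar across access levels.

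**Working it through.** **1. The plan's own figure.** Inputs from Study population: about 2,340 participants, 4% cumulative incidence over 24 months, about 80 events. 2,340 × 0.04 = 93.6. Also 80 / 0.04 = 2,000, and 1 − 2,000/2,340 = 14.5%. So 80 is reproduced if about 14.5% loss is assumed. The article does not state a loss rate and refers to a supplement that is not shown, so 80 is not called wrong. It is used below as the scale, with 93.6 as the upper alternative.

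**2. One participant.** Someone misses months 3, 9 and 15 and attends 6, 12, 18, 21 and 24. That is three absences, which is more than two, so the participant is lost. Dated at the third miss, follow-up ends at month 15 and 9 of 24 months are discarded. Dated at the last attended visit before it, follow-up ends at month 12 and 12 of 24 months are discarded. In both cases an AMI at month 20 is not counted, although the participant was seen at month 18.

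**3. Share of the cohort affected.** Assumptions: each of eight visits is missed independently with probability q, misses are cumulative, and loss is dated at the third miss. The protocol gives no q, so a range is shown.

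- Share lost = 1 − [(1−q)^8 + 8q(1−q)^7 + 28q²(1−q)^6].
- The third miss falls at visit k with probability C(k−1,2) q³ (1−q)^(k−3), and then (8−k)/8 of planned time is discarded. Person-time discarded is the sum over k = 3 to 8.
- The share returning comes from enumerating all 256 attendance patterns.

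| Missed per visit | Lost | Of these, attend a later visit | Person-time discarded |
|---|---|---|---|
| 10% | 1 − (0.4305 + 0.3826 + 0.1488) = 3.8% | 65% | 0.7% |
| 20% | 1 − (0.1678 + 0.3355 + 0.2936) = 20.3% | 67% | 4.3% |
| 25% | 1 − (0.1001 + 0.2670 + 0.3115) = 32.1% | 68% | 7.3% |

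The person-time sum at 20% is 0.0080×5/8 + 0.0192×4/8 + 0.0307×3/8 + 0.0410×2/8 + 0.0492×1/8 = 0.0425.

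**4. Events and precision.** At a constant event rate, the events falling in discarded time are at most about 80 × 0.0069 = 0.5, 80 × 0.0425 = 3.4 and 80 × 0.0729 = 5.8 (0.6, 4.0 and 6.8 if 93.6 is used). Standard errors of log hazard ratios grow by about 1/√(1−0.0425) = 1.02 at 20% missed and 1/√(1−0.0729) = 1.04 at 25%.

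**5. How much the wording decides.** If three consecutive misses were required, the share lost would be q³[1 + (1−q)(3 + (1−q³) + (1−q³(2−q)))]. This gives 0.5%, 4.0% and 7.4% at the same three rates, against 3.8%, 20.3% and 32.1% on the cumulative reading.

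**6. Deaths (secondary).** If a share u of AMIs is not recognised as such, observed HR = true HR × (1−u_poor)/(1−u_good). With a true HR of 1.0:

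- 10% uncaptured in both groups: 0.90/0.90 = 1.00, no bias.
- 10% with good access and 20% with poor: 0.80/0.90 = 0.89.
- 10% with good access and 30% with poor: 0.70/0.90 = 0.78.

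These capture rates are assumptions. The protocol has no data on them.

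**The case against.** The strongest reply is that the definition is loose wording rather than a damaging rule. It does not say that the misses are cumulative, nor that events after return are discarded, and the next sentence keeps telephone and electronic contact open. The person-time at risk is small because a third miss cannot occur before month 9. All of that is fair, and it limits the size of the point. It does not remove it. Since permanent discontinuation is listed separately, the visit alternative must mean something else, and the follow-up rule ends time at loss with no exception for people who return.

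A reader might go further in four ways that the protocol does not support.

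- **That any death censors.** AMI is itself an end point of follow-up, and "All suspected AMI events are adjudicated by an independent, blinded cardiology panel according to the Fourth Universal Definition of Myocardial Infarction (2018"). A fatal AMI recognised as such is an event. Censoring other deaths in a Cox model estimates a cause-specific hazard, which is legitimate. The protocol is silent on unsampled deaths; it does not say that they are censored, and the full protocol may cover them.
- **That missed visits make poor access look protective.** Censoring that is merely more frequent in one access group does not bias that group's Cox hazard ratio. Bias requires missing visits to be related to AMI risk within covariate levels, and the independent-miss calculation above implies none.
- **That 3.8% against 32.1% of participants would be removed from near and remote areas.** These shares count people, who still contribute time until loss. The matching person-time is 0.7% and 7.3%, and attendance by remoteness is not given.
- **That suspected coronary deaths should be added to the primary end point.** This would change the outcome from adjudicated first AMI to a broader one with its own misclassification. It is a design trade-off and does not repair an error.

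**Conclusion.** The point holds for the loss rule. Read together, Study population and Primary outcome analysis end follow-up for participants who miss three of eight visits and return, and leave the date of loss, consecutiveness and the status of remote contact open. The cost is mainly precision: under independent misses dated at the third miss, 0.7% to 7.3% of person-time at 10% to 25% missed per visit, or at most about 0.5 to 6 of 80 events. Bias in hazard ratios is possible but conditional on missed visits being related to AMI risk given the covariates, which the protocol neither shows nor rules out.

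The handling of deaths without blood sampling is a secondary clarification. Any distortion by healthcare access rests entirely on assumed differential capture, and equal capture gives none.

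**What to change.** In Study population and Primary outcome analysis:

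1. Censor at the last date on which AMI-free status is known from clinic visit, telephone or electronic contact, or medical record.
2. State that AMIs in participants who return after missed visits count as events.
3. Treat missed visits as missing covariate data, under the multiple imputation already planned, and not as the end of follow-up. If a missed-visit threshold is kept for monitoring retention, say that it does not affect event follow-up, whether misses must be consecutive, and whether remote contact counts as attendance.

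In Follow-up assessments, as a secondary step: send every death to the existing blinded panel so that a fatal AMI without blood sampling can be recognised, and add a sensitivity analysis for unsampled deaths. The primary end point stays as it is.

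The cost is a few sentences, the recording of a last-known-status date at each contact, and some additional files for the existing panel. The changes should be made before follow-up accumulates, because deaths that went unreviewed and contacts that were not dated are hard to reconstruct later.

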**Methods and analysis:**

This multicentre prospective cohort study will recruit 2,340 adults aged 20–85 years with an estimated 10-year atherosclerotic cardiovascular disease risk ≥20%. Participants will be enrolled from five hospitals in Gansu Province, China, representing variation in ethnicity, altitude, and healthcare access, including Han, Hui, Tibetan, and Kazakh populations. Baseline assessments will include standardized questionnaires, clinical evaluation, and cardiometabolic profiling. Participants will be followed every 3 months for 24 months, with repeated measurements of behavioral, physiological, and biomarker indicators, including wearable electrocardiographic monitoring. Environmental exposures and healthcare accessibility will be assigned using geospatial data. The primary outcome is first incident AMI. Time-to-event models with time-varying variables will be used to examine how within-individual changes in risk indicators are associated with AMI across environmental and ethnic contexts.

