## Introduction

Acute myocardial infarction (AMI) remains a leading cause of mortality worldwide and reflects a major burden of cardiovascular disease at the population level (1). Beyond individual risk factors, environmental conditions and healthcare accessibility play an important role in shaping cardiovascular outcomes. Regional variation in air pollution, climate, altitude, and healthcare resources contributes to differences in cardiovascular risk, highlighting the importance of contextual determinants in public health (2–4).

Ethnic differences further contribute to heterogeneity in cardiovascular risk. Variations in lifestyle, dietary patterns, and social conditions across ethnic groups have been associated with differences in cardiovascular risk profiles and disease burden (5, 6). In western China, populations including Han, Hui, Tibetan, and Kazakh communities are exposed to distinct environmental and social contexts, resulting in heterogeneous cardiometabolic risk patterns (7–9). High-altitude exposure in Tibetan populations is associated with specific physiological adaptations that may influence cardiovascular risk (10).

Despite these insights, most existing studies have focused on long-term risk estimation or cross-sectional comparisons. Commonly used tools, such as the Framingham Risk Score and the China-PAR model, are based on baseline measurements and assume relatively stable risk over time (11–13). Although recent studies have incorporated longitudinal data and time-varying models (14, 15), environmental exposure, healthcare accessibility, and ethnic context are rarely examined simultaneously. As a result, it remains unclear whether short-term risk patterns preceding first AMI differ across populations.

To address this gap, a prospective study integrating environmental exposure, ethnic background, healthcare accessibility, and repeated multidimensional assessment is needed. The present study aims to investigate the short-term risk of first AMI in a multiethnic cohort and to examine how environmental and ethnic differences are associated with variation in short-term cardiovascular risk. By focusing on population-level heterogeneity and within-individual changes over time, this study seeks to provide a more context-sensitive understanding of cardiovascular risk and to inform targeted prevention strategies.

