The study is particularly distinctive in its explicit focus on environmental and ethnic differences as sources of heterogeneity in short-term risk. Cardiovascular risk is influenced by geographic context, healthcare accessibility, and social conditions (2, 4). In China, ethnic disparities in cardiovascular risk factors and disease burden have been widely documented and are associated with differences in lifestyle, diet, and social determinants of health (5, 6) Kazakh populations have distinct cardiometabolic profiles (7, 8), and studies in Hui populations have reported differences in health behaviour and information-seeking patterns (42). Tibetan populations living at high altitude exhibit physiological characteristics related to hypoxic adaptation (10), and recent studies have described population-specific adaptation mechanisms (32). These ethnic differences coexist with environmental heterogeneity, including variation in altitude, air pollution, and healthcare accessibility. Environmental exposures such as particulate matter and meteorological variation have been associated with cardiovascular outcomes (3), and high-resolution datasets enable spatial characterization of environmental exposures and healthcare accessibility across China (32, 33). These population and environmental differences suggest that similar changes in symptoms, behaviors, physiological measurements, or biomarkers may not correspond to the same degree of short-term risk. Interpretation of changes before first AMI may therefore depend on the environmental and population context in which they occur. Future findings from this study may indicate whether risk progression before first AMI follows common patterns or differs across populations.

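### The prespecified Cox model adjusts ethnicity for blood pressure, diabetes, lipids and smoking, so its hazard ratio is what remains after measured risk factors and can misstate the population difference the study asks about

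*Protocol article*

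**What the plan says.** The Primary outcome analysis section sets the method: "Associations between baseline variables and time to first incident AMI will be evaluated using Cox proportional hazards regression models". It then fixes the covariates: "Multivariable models will include prespecified variables, including age, sex, ethnicity, smoking status, systolic blood pressure, diabetes status, lipid profile, and environmental exposures". Ethnicity and environmental exposures thus enter alongside smoking, systolic pressure, diabetes and lipids. No single exposure is designated.

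The aim in the Introduction is "to examine how environmental and ethnic differences are associated with variation in short-term cardiovascular risk". Study design repeats it in similar terms. Outcomes describes the primary outcome as "allowing assessment of variation in near-term risk across populations with different environmental exposures, ethnic backgrounds, and healthcare accessibility". The abstract puts a different question, namely "how within-individual changes in risk indicators are associated with AMI across environmental and ethnic contexts".

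On how groups come to differ, the Introduction describes the four communities as "exposed to distinct environmental and social contexts, resulting in heterogeneous cardiometabolic risk patterns". The Discussion adds that "ethnic disparities in cardiovascular risk factors and disease burden have been widely documented and are associated with differences in lifestyle", together with diet and social determinants. Baseline variables lists smoking among the lifestyle variables.

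**The concern.** Asking whether AMI risk differs between populations is asking for a contrast between groups. If groups differ in risk partly because their blood pressure, lipids, diabetes or smoking differ, a model holding those factors fixed answers another question: how much difference is left among people with the same measured risk factors. Both questions are legitimate, but they have different answers, and the article does not say which one its ethnicity hazard ratio addresses.

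At stake is interpretation. An ethnic difference that runs mainly through cardiometabolic factors could appear as a hazard ratio near 1 and be read as absence of a population difference. With about 80 expected events, such a reading would be hard to dispel afterwards.

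**Working it through.** **1. Are the adjusted factors downstream on the article's own account?** For ethnicity, largely yes. The Introduction has context producing cardiometabolic patterns and links ethnic differences in risk profile to lifestyle and diet. The Discussion speaks of ethnic disparities in the risk factors themselves and of distinct Kazakh cardiometabolic profiles. Systolic pressure, diabetes and lipids are cardiometabolic factors, and smoking is classed as lifestyle. For environmental exposures the text is thinner: the Discussion links particulate matter and weather to outcomes without giving a route.

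**2. Does another described analysis give the population contrast?**
- The general group comparisons (analysis of variance, Kruskal–Wallis, chi-square) are not age-adjusted and do not handle censoring.
- The time-varying Cox models estimate associations of updated measurements with AMI.
- The heterogeneity analysis asks whether an exposure's association differs by subgroup, and places its interaction terms in multivariable models.
- The trajectory comparisons in Outcomes concern markers, not AMI risk.

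None is an age- and sex-adjusted time-to-event contrast between populations.

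**3. The article's event count.** 2,340 × 0.04 = 93.6, against about 80 stated. With 14.5% attrition, 2,340 × 0.855 × 0.04 = 80.0. The article gives no attrition rate and refers to a supplement that is not shown, so the figure is neither confirmed nor wrong. I use 80 below.

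**4. Size of the shift.** Let m be the share of the log hazard ratio that runs through the adjusted factors. Approximately, HR_adjusted = HR_total^(1 − m). The documents give neither HR_total nor m; both are assumed.

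| Assumed total HR | m = 25% | m = 50% | m = 75% |
|---|---|---|---|
| 1.5 | 1.36 | 1.22 | 1.11 |
| 2.0 | 1.68 | 1.41 | 1.19 |

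The shift can go the other way. If direct and indirect effects oppose each other, m is negative: at m = −50%, 1.5^1.5 = 1.84, so adjustment enlarges the hazard ratio.

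**5. What this does to detectability.** Midpoints of the ethnic targets are Han 975, Hui 700, Tibetan 450 and Kazakh 300, total 2,425. Splitting 80 events in proportion gives 80 × 1,675/2,425 = 55.3 for Hui against Han, 80 × 1,425/2,425 = 47.0 for Tibetan and 80 × 1,275/2,425 = 42.1 for Kazakh. Power at two-sided 0.05 is Φ(|ln HR| × √(d·p·(1 − p)) − 1.96), where d is events and p the minority fraction of the pair. For Hui at HR 2.0: p = 700/1,675 = 0.418, √(55.3 × 0.418 × 0.582) = 3.67, and 0.693 × 3.67 − 1.96 = 0.58, which gives 72%.

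| Contrast with Han | Total HR 2.0 | Half mediated (1.41) | Total HR 1.5 | Half mediated (1.22) |
|---|---|---|---|---|
| Hui | 72% | 25% | 32% | 11% |
| Tibetan | 60% | 20% | 25% | 9% |
| Kazakh | 48% | 16% | 20% | 8% |

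The fall reflects a smaller quantity being estimated, not a loss of efficiency.

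**6. Simulation, with and without selection at entry.** The set-up was a binary group (40%), one mediator, age, a total HR of 1.5, two years of follow-up and an event rate of about 4% to 5%. Cox models were fitted without and with the mediator. The selected runs kept only people above a threshold on a score built from age and the mediator.

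| Mediated share | Unselected: without / with mediator | Selected: without / with mediator |
|---|---|---|
| 50% | 1.53 / 1.26 | 1.41 / 1.24 |
| 100% | 1.52 / 1.00 | 1.33 / 1.03 |

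Selection lowers the mediator-free hazard ratio too, so leaving the mediators out does not recover 1.5.

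**The case against.** The strongest reply is that the section covers baseline variables generally, and mutual adjustment is proper for most of them. It speaks of multivariable models in the plural and does not rule out unadjusted or age- and sex-adjusted fits, which an analysis plan often supplies. The abstract's question is effect modification, which the heterogeneity section addresses. Much of this stands. A reader might infer that the plan excludes a staged analysis; the text does not say so. What remains is that the one covariate set it does state does not match the population contrast in the Introduction and Outcomes, and its hazard ratio is not labelled as conditional.

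A reader might also infer that the plan names these four factors as the pathways for both ethnicity and environment. It does not. It speaks of cardiometabolic patterns and lifestyle, mostly in terms of association. Nothing makes smoking an intermediate for altitude or pollution, where it is more plausibly a confounder. A first-stage environmental model with only age and sex would be confounded as well, because ethnicity and altitude vary together across sites: the predominantly Tibetan and Kazakh centres are at 3,369 m and 3,289 m, the other three at 2,098 m to 2,282 m.

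Finally, low power does not come only from adjustment. At a total HR of 1.5 no pairwise contrast exceeds 32% power, so a null result is likelier than not under either model.

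**Conclusion.** The point holds in a limited form. The ethnicity hazard ratio from the stated model is the difference remaining after measured risk factors, and it can attenuate or distort the population difference the study sets out to examine. The point is strongest for ethnicity. For environmental exposures it concerns only plausible intermediates: systolic pressure, diabetes and lipids.

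It is tempting to conclude that the model will hide real differences. The documents do not support that certainty, because the mediated share is unknown and the distortion can run in either direction. The figures are illustrations under assumed total hazard ratios, assumed mediated shares, an event split proportional to the recruitment midpoints, and an entry score assumed to contain the mediators. Nor should a mediator-free model be read as the total population effect, since entry requires a predicted 10-year risk of at least 20%. This is worth correcting in the analysis section, but it does not undermine the study design.

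**What to change.** In Primary outcome analysis, prespecify staged models and state what each estimates.

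- **Ethnicity, stage 1:** age and sex, without systolic pressure, lipids, diabetes and smoking. Report it as the ethnic contrast among people entering at a predicted 10-year risk of at least 20%. It will include differences in altitude and site that accompany ethnicity, and should be described so.
- **Ethnicity, stage 2:** the current covariate list, labelled as the part not explained by measured risk factors. Because that list also contains environmental exposures, the label should mention them.
- **Environmental exposures, stage 1:** keep the confounders (age, sex, ethnicity, smoking, socioeconomic status) and leave out only the plausible intermediates (systolic pressure, diabetes, lipids).
- **Environmental exposures, stage 2:** add those intermediates and label the result in the same way.

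Report both stages and interpret each for its own question, without resting conclusions on stage 1 alone. State that selection on predicted risk means neither stage is the total effect in the general population. The current adjusted model stays in use for the other baseline variables. If a staged analysis already exists in an analysis plan, one clarifying sentence is enough.

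The cost is a short addition to the text and one extra fitted model per contrast, with no new data. The downside is that the contrast remains limited to the selected cohort.
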